## 8.2 Descriptive Analysis

Descriptive attributes of vaccinated and unvaccinated cohorts will be presented as absolute numbers and percentages. We will use a  $\chi^2$  test to test for significant differences in the distribution of the categorical covariates among individuals between each of the vaccinated and unvaccinated cohorts at cohort entry. Continuous variables will be presented as the mean with standard deviation and/or median with interquartile ranges, with p-values for the two-sample t-test or Wilcoxon rank-sum test, as appropriate. Absolute standardized differences will be calculated to assess the balance of covariates.

Overall incidence rates of COVID-19 diagnosis and of severe COVID-19 for the vaccinated and unvaccinated cohorts will be calculated by dividing the number of incident events by the total number of person-years.

## 8.3 Primary Analyses

The primary analyses addressing Primary Objectives 1-2 will be conducted at interim and final analyses (Figure 1).

Unadjusted hazard ratios (HR) and adjusted HR and confidence intervals (CIs) comparing COVID-19 diagnosis or severe COVID-19 disease in vaccinated and unvaccinated individuals will be estimated by Cox proportional hazards regression models without and with adjustment for potential confounders described in Section 7.3. Unadjusted VE (%) will be calculated as  $(1 - \text{unadjusted HR}) \times 100$ . Adjusted VE (%) will be calculated as  $(1 - \text{adjusted HR}) \times 100$ . For final analysis of primary objectives, we may also conduct propensity score analyses with inverse probability of treatment weighting (IPTW) to balance covariates across exposure groups.

For each interim analysis and final analysis, the test significance level will be adjusted using an alpha spending approach without a stopping rule (similar to the Bonferroni correction,  $p=0.007=0.05/7$ ). This is a conservative approach to keep the overall Type I error below 0.05. As such, we will be calculating 99.3% CIs for each interim and final analysis. We will provide 95% CIs for each analysis as well.

## 8.4 Secondary Analyses

Secondary analyses will be conducted for the 4th interim and the final analysis. Select secondary analyses will also be conducted for the 1st interim analysis (VE by age, sex, race/ethnicity, history of COVID-19, and asymptomatic COVID-19 [based on individuals with a positive result from a surveillance/asymptomatic test]) and for the 2nd interim analysis (VE in pregnant women).

For each secondary analysis, we will examine the distribution of index dates in vaccinated individuals; we will assign index dates by stratified variables so that the frequency distribution of their index dates matches that of vaccinated individuals.

**Secondary Objective 1:** For Secondary Objective 1, analyses will be stratified by sex and age category (12-17 years, 18-44 years, 45-64 years, 65-74 years, and 75+ years) at index date. For each stratum, we will calculate COVID-19 diagnosis incidence, unadjusted and adjusted HRs and VEs, as described for the primary analysis above.

**Secondary Objective 2:** For Secondary Objective 2, analyses will be stratified by race/ethnicity (Non-Hispanic White, Non-Hispanic Black, Hispanic, and Non-Hispanic Asian). For each stratum, we will calculate COVID-19 diagnosis incidence, unadjusted and adjusted HRs and VEs, as described for the primary analysis above.

**Secondary Objective 3:** For Secondary Objective 3, analyses will include individuals with chronic diseases (e.g., chronic kidney disease, lung disease including COPD and asthma, diabetes, identified by ICD-10 codes). For each disease, we will calculate COVID-19 diagnosis incidence, unadjusted and adjusted HRs and VEs, as described for the primary analysis above.

**Secondary Objective 4:** For Secondary Objective 4, analyses will include individuals who are immunocompromised (e.g., HIV, cancer, transplant, immunosuppressive medications identified by ICD-10 codes, registries, and pharmacy data). We will calculate COVID-19 diagnosis incidence, unadjusted and adjusted HRs and VEs, as described for the primary analysis above.

**Secondary Objective 5:** For Secondary Objective 5, analyses will include individuals with autoimmune conditions (e.g., rheumatoid arthritis, inflammatory bowel disease, psoriasis, psoriatic arthritis, multiple sclerosis, systemic lupus erythematosus). We will calculate COVID-19 diagnosis incidence, unadjusted and adjusted HRs and VEs, as described for the primary analysis above.

**Secondary Objective 6:** For Secondary Objective 6, analyses will include individuals who are frail, identified using the method by Kim et al.[15] We will calculate COVID-19 diagnosis incidence, unadjusted and adjusted HRs and VEs, as described for the primary analysis above.

**Secondary Objective 7:** For Secondary Objective 7, analyses will include pregnant women. We will calculate COVID-19 diagnosis incidence, unadjusted and adjusted HRs and VEs, as described for the primary analysis above.

**Secondary Objective 8:** For Secondary Objective 8, analyses will include individuals with a history of COVID-19 diagnosis. Incident COVID-19 diagnosis (a COVID-19 reinfection, >90 days after the most recent prior COVID-19 diagnosis code or SARS-CoV-2 positive molecular test) during follow-up will be assessed using two definitions. The first definition will require a COVID-19 diagnosis code with chart-confirmed symptoms or a SARS-CoV-2 positive molecular test. The second, more specific definition will require a COVID-19 diagnosis code with chart-confirmed symptoms, a SARS-CoV-2 positive molecular test with chart-confirmed symptoms, or a SARS-CoV-2 positive molecular test with an intervening SARS-CoV-2 negative molecular test. We will calculate COVID-19 diagnosis incidence, unadjusted and adjusted HRs and VEs, as described for the primary analysis above.

**Secondary Objective 9:** CDC initially recommended that COVID-19 vaccines be routinely administered alone, with a minimum interval of 14 days before or after administration with any other vaccine. In May 2021, CDC updated their recommendations to indicate that COVID-19 vaccines and other vaccines may be administered without regard to timing; this includes administration of COVID-19 vaccines and other vaccines on the same day as well as within 14 days of each other. For Secondary Objective 9, we will compare individuals who received either the first or second dose of Moderna COVID-19 vaccine concomitantly with another vaccine (i.e., on the same day) with unvaccinated individuals. We will calculate COVID-19 diagnosis incidence and unadjusted and adjusted HRs and VEs, as described for the primary analysis above.

**Secondary Objective 10:** For Secondary Objective 10, we will calculate VE of 2 doses of Moderna COVID-19 vaccine against asymptomatic COVID-19. We will calculate the incidence of asymptomatic COVID-19 and estimate unadjusted and adjusted HRs and VEs, as described for the primary analysis above.

**Secondary Objective 11:** For Secondary Objective 11, we will calculate VE of 2 doses of Moderna COVID-19 vaccine against symptomatic COVID-19. We will calculate the incidence of symptomatic COVID-19 and estimate unadjusted and adjusted HRs and VEs, as described for the primary analysis above.

**Secondary Objective 12:** For Secondary Objective 12, we will estimate the VE against COVID-19 diagnosis by year. We will calculate COVID-19 diagnosis incidence by follow-up year by dividing the number of incident events occurring within that year by the number of person-years of follow-up for individuals at risk in that year. We will use time-varying Cox regression models to estimate unadjusted and adjusted HRs and VEs, for follow-up Year 1, Year 2, and Year 3 after the index date.

**Secondary Objective 13:** For Secondary Objective 13, we will estimate the VE against severe COVID-19 by year. We will calculate severe COVID-19 incidence, unadjusted and adjusted HRs and VEs, as described for the Secondary Objective 12 analysis above, for follow-up Year 1, Year 2, and Year 3 after the index date.

**Secondary Objective 14:** For Secondary Objective 14, we will estimate the VE against COVID-19 diagnosis among those who only received 1 dose of Moderna COVID-19 vaccine compared to unvaccinated individuals. We will calculate COVID-19 diagnosis incidence, unadjusted and adjusted HRs and VEs, as described for the primary analysis above.

**Secondary Objective 15:** For Secondary Objective 15, we will estimate the VE against severe COVID-19 among those who only received 1 dose of Moderna COVID-19 vaccine compared to unvaccinated individuals. We will calculate severe COVID-19 incidence, unadjusted and adjusted HRs and VEs, as described for the primary analysis above.

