| Other variables                                                                                             |                                     |
| KPSC physician/employee status at index date                                                                       | Yes, No                             |
| Frailty index in year prior to index date (-365 to -1 day, inclusive), using method by Kim et al. [15]             | To be determined based on quartiles |
| History of COVID-19 diagnosis (from March 1, 2020 to index date, inclusive)                                        | Yes, No                             |
| History of SARS-CoV-2 molecular test performed (from March 1, 2020 to index date, inclusive), regardless of result | Yes, No                             |
| Concomitant vaccine                                                                                                | Yes, No                             |
| Immunocompromised status                                                                                    | Yes, No                             |
| HIV/AIDS any time prior to index date                                                                              | Yes, No                             |
| Leukemia, lymphoma, congenital immunodeficiencies, asplenia/hyposplenism any time prior to index date              | Yes, No                             |
| Organ transplant any time prior to index date                                                                      | Yes, No                             |
| Immunosuppressant medications at index date                                                                        | Yes, No                             |

\* Charlson comorbidities include myocardial infarction, congestive heart failure, peripheral vascular disease, cerebrovascular disease, connective tissue disease, dementia, chronic pulmonary disease, connective tissue disease, peptic ulcer disease, diabetes mellitus, paraplegia and hemiplegia, renal disease, liver disease, cancer, metastatic solid tumor, human immunodeficiency virus (HIV), and acquired immunodeficiency syndrome (AIDS)

The covariates included in adjusted analyses will be determined by scientific relevance, association with exposure, and data availability. Specifically, we will select covariates by following these steps:

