1. The distribution of covariates will be reviewed. Some categories of a categorical variable with small sample sizes may be redefined or combined into one category.
2. The association of baseline covariates with exposure will be assessed. We will use standardized difference to assess the balance of covariates between exposed and unexposed cohorts. Unlike p-values, for which magnitude is highly related to sample size, standardized difference is a unified approach to quantifying the magnitude of difference between groups regardless of sample size, where an absolute value less than 0.1 is considered a negligible difference. Potential confounders will be determined by absolute standardized difference (ASD) >0.1.
3. All potential confounders from Step 2 will be included in the analyses. Steps 1 and 2 will be repeated for the 2-dose cohort and the 1-dose cohort. Matching variables (age, sex, race/ethnicity and index date), which are considered important risk factors, will be kept in the

adjusted model for possible imbalance on matching variables due to loss to follow-up or subgroup analysis (e.g., by baseline comorbidities).

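### Secondary Objective 8 plans no covariate for time since prior infection, so VE in the previously infected may be confounded, in an unknown direction

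*Protocol*

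**What the plan says.** Protocol Section 8.4 defines the population for this objective: "For Secondary Objective 8, analyses will include individuals with a history of COVID-19 diagnosis". A reinfection counts only if it falls ">90 days after the most recent prior COVID-19 diagnosis code or SARS-CoV-2 positive molecular test". For the estimate itself the section refers back: "We will calculate COVID-19 diagnosis incidence, unadjusted and adjusted HRs and VEs, as described for the primary analysis above". That analysis (Section 8.3) is a Cox model adjusted for the confounders of Section 7.3.

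Table 3 in Section 7.3 holds two variables on past infection or testing, both coded Yes/No:
- "History of COVID-19 diagnosis (from March 1, 2020 to index date, inclusive")
- "History of SARS-CoV-2 molecular test performed (from March 1, 2020 to index date, inclusive), regardless of result"

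Selection is described in the same section: "The covariates included in adjusted analyses will be determined by scientific relevance, association with exposure, and data availability". The working rule is "Potential confounders will be determined by absolute standardized difference (ASD) >0.1", and "Steps 1 and 2 will be repeated for the 2-dose cohort and the 1-dose cohort". The Objective 8 subgroup is not named there. The matching variables are age, sex, race/ethnicity and index date.

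Section 8.4 schedules the analysis by history of COVID-19 for the first interim, and all secondary analyses for the fourth interim and the final analysis. The protocol gives no sample size, event rate or target VE for Objective 8.

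**The concern.** Restricting to people with a history of COVID-19 sets the history variable to Yes for everyone, so it can adjust for nothing. What still varies is how long ago the infection occurred. If protection after infection wanes, that interval affects the reinfection rate. If it also differs between recipients and comparators, it confounds the hazard ratio. Nothing listed would pick this up.

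A second issue comes from the 90-day rule. The history window runs up to and including the index date, and Section 6.1 has no exclusion for recent infection. Someone infected shortly before index can enter, yet for up to about three months no event of theirs can count. If that time is treated as time at risk, it lowers the rate in whichever arm holds more recently infected people.

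At stake is the VE estimate for one secondary subgroup, reported from the first interim onward.

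**Working it through.** There is no stated figure for Objective 8 to reproduce. The check has four steps, and every share and hazard below is an assumption.

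**1. Does any planned variable carry the interval?**
- History of diagnosis: constant at Yes.
- History of any molecular test: Yes/No, regardless of result, no date.
- Month of index date, and matching on index date: these align calendar time. Two people with the same index date can still have been infected at very different times.
- Possible interval at index: 0 to 395 days at the first interim (1 March 2020 to 31 March 2021) and 0 to 670 days at the end of accrual (31 December 2021).

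No planned variable carries it.

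**2. Confounding by the interval**

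Observed HR = true HR × (mean baseline reinfection hazard in recipients ÷ the same in comparators).

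Assume hazards relative to naive of 0.10 (infected under 6 months ago) and 0.20 (6–12 months). Only their ratio matters.

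- Comparators 60% recent: 0.6 × 0.10 + 0.4 × 0.20 = 0.14
- Recipients 40% recent: 0.4 × 0.10 + 0.6 × 0.20 = 0.16
- Factor: 0.16 / 0.14 = 1.143

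| Recent share, comparators / recipients | Factor | True VE 60% reads | True VE 40% reads |
|---|---|---|---|
| 50% / 40% | 0.16/0.15 = 1.067 | 57.3% | 36.0% |
| 60% / 40% | 0.16/0.14 = 1.143 | 54.3% | 31.4% |
| 70% / 40% | 0.16/0.13 = 1.231 | 50.8% | 26.2% |
| 40% / 60% (reversed) | 0.14/0.16 = 0.875 | 65.0% | 47.5% |
| equal shares | 1.000 | 60.0% | 40.0% |

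For example, 1 − 0.40 × 1.143 = 0.543.

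**3. The 90-day rule alone, with no waning assumed**

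Assume follow-up from day 14 to day 120 after index (Section 9 uses an average of 4 months for the first interim), infections among the recently infected spread evenly over the 90 days before index, and all time from day 14 counted as at risk.

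- Mean days in which no event can count: 76² / (2 × 90) = 32.1 of 106.
- Event rate of the recently infected relative to others: r = 1 − 32.1/106 = 0.697.
- Factor = (fv × r + 1 − fv) / (fu × r + 1 − fu), where fv and fu are the shares of recipients and comparators infected within 90 days before index.

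| fv / fu | Factor | True VE 50% reads |
|---|---|---|
| 10% / 30% | 1.067 | 46.7% |
| 10% / 50% | 1.143 | 42.9% |
| 50% / 10% | 0.875 | 56.2% |
| equal | 1.000 | 50.0% |

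This is a rate-ratio approximation to the Cox estimate.

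**4. Would the protocol's own screen have selected the variable?**

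For recent shares of 20% against 25%, ASD = 0.05 / √[(0.20 × 0.80 + 0.25 × 0.75)/2] = 0.05 / 0.417 = 0.12, above the 0.1 threshold. Even this modest imbalance would be caught if the variable were screened.

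**The case against.** **The covariate set of one secondary model belongs in the analysis plan, and the list is not closed.** This is the strongest point. Table 3 lists possible covariates, selection may rest on scientific relevance, and Table 6 schedules a separate statistical analysis plan. It stands to this extent: adding the interval is permitted. But the protocol itself sets the covariates, their categories, the look-back windows and the selection steps, and then applies the primary-analysis process to a subgroup in which its prior-infection term is empty.

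**The documents give no evidence of imbalance.** This stands in full, and it is why the point is a risk and not a demonstrated bias. A reader might infer that the interval must differ by arm because recipients needed two doses at least 24 days apart. The documents do not support that. The history window runs to the index date in both arms, infection between doses is not excluded, and the dose spacing bears at most on the few weeks before index. It does not imply a 60/40 split at six months.

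**Timing is already partly handled.** Index dates are aligned, and the 90-day rule applies to both arms. Both are true. Alignment equalises calendar time but not time since infection, and the 90-day rule governs which events count without balancing the interval or stating when risk time begins. Section 13 acknowledges unmeasured differences between the cohorts, but this interval is measurable.

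**It is one of 17 secondary objectives, declared possibly underpowered.** This is true and limits the weight of the point.

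**Conclusion.** The point holds as a gap in planned confounding control. In Objective 8 the only prior-infection covariate is constant, and time since the most recent infection is neither listed nor matched on. VE in the previously infected may be confounded by it, in a direction the documents do not allow one to predict. With a balanced interval there is no such bias.

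Under the assumed hazards and splits in step 2, a true VE of 60% reads anywhere from 50.8% to 65.0%. The 90-day rule alone, under the assumptions of step 3, moves a true VE of 50% to between 42.9% and 56.2%. These ranges show what an imbalance could do. They do not forecast the error, since no share or hazard in them comes from the protocol.

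The unstated start of risk time for people infected within 90 days before index is a related gap in the same objective. The change is worth making because the date is already needed and the comparison is observational. The primary analyses are not touched.

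**What to change.** For Secondary Objective 8:
1. Derive days from the most recent COVID-19 diagnosis code or positive molecular test to the index date, and add it to Table 3 for this objective.
2. Include it in the adjusted Cox model as a spline, or as categories suited to the data at each analysis. Fixed cut-points may fail early: at the first interim the longest possible interval is 395 days, so a category above 365 days would be nearly empty.
3. Report its distribution and ASD by arm within the subgroup.
4. State that risk time starts at the later of day 14 after index and day 91 after the prior infection. Adjustment alone would leave in person-time during which no event can count.

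The cost is one derived covariate, from a date the reinfection definition already requires, and slightly less person-time.

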## 5 Study Design Overview

We will conduct an observational cohort study to evaluate the VE of Moderna COVID-19 vaccine in preventing COVID-19 diagnosis and severe COVID-19. Vaccine exposure, COVID-19 outcomes, and covariates will be identified from EHR, as described in Section 7 below. All individuals who receive Moderna COVID-19 vaccine from December 2020 to December 2021 and meet eligibility criteria specified in Section 6.1 below will be included in the study (“vaccinated”, hereafter). The unvaccinated comparator cohort will comprise individuals who have not received Moderna COVID-19 vaccine or any other COVID-19 vaccine as of the index date of their matched vaccinated individual (see Section 6.2 for details on index date) and who meet eligibility criteria specified in Section 6.1 below. Unvaccinated individuals who subsequently receive Moderna COVID-19 vaccine may contribute person-time to both unvaccinated and vaccinated cohorts. Individuals will be followed up through EHR for occurrence of COVID-19 outcomes until the end of the study period (December 31, 2023 for final analysis), or censoring events (termination of KPSC membership allowing for a 31-day gap, death, receipt of a COVID-19 vaccine).

Six interim analyses and a final analysis will be conducted. For the first and second interim analyses, unvaccinated individuals will be randomly selected and n:1 matched to vaccinated individuals by age, sex, and race/ethnicity (if sample size allows), and will be assigned an index date based on the vaccination date of their matched vaccinated individual. For subsequent interim analyses and the final analysis, the number of eligible unvaccinated individuals in the KPSC population may be insufficient for individual matching; if so, frequency matching will be employed. In all analyses, efforts will be dedicated to identifying and adjusting for potential confounders. Cox proportional hazards regression will be used to estimate unadjusted and adjusted HRs. VE (%) will be estimated as  $(1 - \text{adjusted HR}) \times 100$ . Propensity score analyses with inverse probability of treatment weighting (IPTW) will be considered for final analyses.

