|                                                      | 2                                                               | 70                         | >.999 |
| 1 vs 0.5                                             | 0.3                                                             | 90                         | 0.84  |
|                                                      | 0.3                                                             | 80                         | 0.69  |
|                                                      | 0.3                                                             | 70                         | 0.51  |
| 1 vs 1                                               | 0.3                                                             | 90                         | 0.93  |
|                                                      | 0.3                                                             | 80                         | 0.81  |
|                                                      | 0.3                                                             | 70                         | 0.62  |
| 1 vs 5                                               | 0.3                                                             | 90                         | 0.99  |
|                                                      | 0.3                                                             | 80                         | 0.97  |
|                                                      | 0.3                                                             | 70                         | 0.82  |

Based on the current Moderna COVID-19 vaccine implementation plan and anticipated uptake, we expect to accrue 500,000 to 1,000,000 individuals receiving 2 doses of Moderna COVID-19 vaccine for analyses of primary objectives by the end of 2021.

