### Statistical Analysis

Separate analyses will be conducted using the TND for 2-dose and 1-dose VE.

For each VOC or VOI, characteristics of test-positive cases and their matched test-negative controls will be described and compared. Specimens with unsuccessful sequencing may also be considered a test-positive case group for analysis. Continuous covariates such as age in years will be summarized by mean, standard deviation, median, quartiles, minimum, and maximum value, and compared using t-test or Wilcoxon rank-sum test, as appropriate; categorical covariates will be summarized by frequency and percentage and compared using chi-square test or Fisher's exact test, as appropriate. Absolute standardized difference will be calculated to assess the balance of covariates. Potential confounders will be determined based on bivariate analyses and scientific relevance. Given the small sample size and possible need to limit the number of covariates in an adjusted model, potential confounders will be determined by absolute standardized difference (ASD)  $> 0.1$  and  $p\text{-value} < 0.1$ , or scientific relevance.

Conditional logistic regression will be used to estimate the odds ratio (OR) and confidence intervals (CIs) of being vaccinated among cases vs controls, without and with adjustment for potential confounders determined from bivariate analyses. VE (%) will be calculated as  $(1 - \text{OR}) \times 100$ .

The TND analysis will be performed for both an interim analysis and a final analysis. For each interim analysis and final analysis, the test significance level will be adjusted using the Bonferroni correction,  $p = 0.025$  ( $= 0.05/2$  tests). As such, we will be calculating 97.5% CIs for each interim and final analysis. We will provide 95% CIs for each analysis as well. If sample

sizes allow, separate analyses using the same methods described above will be considered for VOCs and VOIs associated with severe COVID-19 disease (COVID-19 hospitalization).

For selected VOCs (e.g., Delta variant), if sample sizes allow, separate analyses will be conducted to assess the VE of Moderna COVID-19 vaccine against SARS-CoV-2 variants by time since most recent Moderna COVID-19 vaccination using the methods similar to those described above. Matching possibly will not be maintained in the subgroup analyses. Matching variables (age, sex, and race/ethnicity) and month of specimen collection will be kept in the adjusted model.

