## 11 Timelines

Table 6. Estimated Project Timelines

| Description                                                                                                                                   | Estimated timeline    |
|-----------------------------------------------------------------------------------------------------------------------------------------------|-----------------------|
| Contract executed                                                                                                                             | 01/28/2021            |
| KPSC to submit protocol to Moderna                                                                                                            | 02/09/2021            |
| KPSC to obtain IRB approval                                                                                                                   | 04/30/2021            |
| KPSC to submit final Project Management Plan to Moderna                                                                                       | 05/30/2021            |
| KPSC to submit final Data Management and Statistical Analysis Plan to Moderna                                                                 | 06/16/2021            |
| Vaccinated individuals accrual                                                                                                                | 12/18/2020-12/31/2021 |
| End of follow-up                                                                                                                              | 12/31/2023            |
| KPSC to submit first interim analysis manuscript to Moderna
(Vaccination between 12/18/2020-3/31/2021)                                     | 08/31/2021            |
| KPSC to submit variant VE manuscript to Moderna (interim results)
(Specimen collection between March 2021-July 2021)                       | 10/31/2021            |
| KPSC to submit second interim analysis report (or manuscript if deemed appropriate) to Moderna
(Vaccination between 12/18/2020-6/30/2021)  | 11/30/2021            |
| KPSC to submit third interim analysis report (or manuscript if deemed appropriate) to Moderna
(vaccination between 12/18/2020-9/30/2021)   | 02/28/2022            |
| KPSC to submit final variant VE manuscript to Moderna
(Specimen collection between 03/04/2021-02/28/2022)                                  | 06/30/2022            |

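### The cohort durability analyses (Secondary Objectives 12-13) give one hazard ratio per follow-up year, so any waning within the first 12 months after dose 2 is averaged into a single value per outcome

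*Protocol*

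**What the plan says.** Protocol section 8.4 defines durability against COVID-19 diagnosis (Secondary Objective 12) through a time-varying Cox model that yields one hazard ratio, and hence one VE, "for follow-up Year 1, Year 2, and Year 3 after the index date". For Secondary Objective 13 the same approach applies: "we will estimate the VE against severe COVID-19 by year". Neither objective has a narrower interval, a spline or a continuous function of time.

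Other provisions that bear on the point:

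- **Follow-up.** Section 11 gives the accrual window as "12/18/2020-12/31/2021". Section 5 ends follow-up on "December 31, 2023 for final analysis" "or censoring events (termination of KPSC membership allowing for a 31-day gap, death, receipt of a COVID-19 vaccine". A further dose therefore ends a two-dose recipient's follow-up.
- **Timing.** Section 8.4 places the secondary analyses at the 4th interim and the final analysis. The few brought forward to the 1st and 2nd interims do not include durability.
- **A finer analysis elsewhere.** For Secondary Objectives 16-17, section 10.1 says: "For selected VOCs (e.g., Delta variant), if sample sizes allow, separate analyses will be conducted" to estimate VE "by time since most recent Moderna COVID-19 vaccination". Section 10.3 ends the specimens for that work in February 2022.

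**The concern.** A durability objective asks when, and by how much, protection falls. With one coefficient for the whole first year, the model cannot show any change before month 12. The Year 1 value describes neither early nor late protection in that year. A decline appears only as a difference between Year 1 and Year 2.

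This costs most at the 4th interim. Few people will have entered Year 2 by then and nobody will have reached Year 3, so the first durability report would be close to a single overall VE for each outcome.

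**Working it through.** The protocol states no person-time, power or expected estimate for Secondary Objectives 12-13, so there is no figure of its own to reproduce. The check has two parts.

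**1. Share of person-time by follow-up year**

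Inputs from the protocol:
- Accrual starts 18 December 2020 (section 11) and the doses are at least 24 days apart (section 7.1), so the earliest second dose is 11 January 2021. The latest is 31 December 2021, 354 days later.
- Outcomes count from day 14 (section 7.2).
- Follow-up ends 31 December 2023, which is 1,084 days after 11 January 2021.
- Retention is above 90% at one year and above three-quarters at three years (section 4).

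Assumptions: second-dose dates are uniform over the window, and a further dose censors nobody unless stated.

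Final analysis, no disenrolment:
- Mean days at risk = 1,084 − 354/2 − 14 = 893.
- Year 1: 365 − 14 = 351 days; 351/893 = 39%.
- Year 2: 365/893 = 41%.
- Year 3: 893 − 351 − 365 = 177 days; 177/893 = 20%.

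With exponential disenrolment at −ln(0.75)/3 = 0.096 per year, the shares are 42%, 40% and 18%. At −ln(0.9) = 0.105 per year, Year 1 is still 42%. If second doses instead fall in February to June 2021, Year 1 holds 36-39%.

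4th interim: the text at hand gives no data cut (Figure 1 is not shown), so a range is assumed. With D days from 11 January 2021 to the cut, mean time at risk is D − 177 − 14. Mean Year 2 time is (D − 365)²/(2 × 354).

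| Assumed cut | D | Mean days at risk | Mean Year 2 days | Year 1 share |
|---|---|---|---|---|
| 31 March 2022 | 444 | 253 | 8.8 | 96% |
| 30 June 2022 | 535 | 344 | 40.8 | 88% |
| 30 September 2022 | 627 | 436 | 97.0 | 78% |

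Year 3 is empty in every row.

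Further-dose censoring at the final analysis: uptake is not given, so it was varied from 0% to 100%, spread over days 150-365 or 180-300. Year 1 passes 50% of person-time only when about 33-46% or more of recipients are censored this way. At 50% uptake the share is 52-56%; at 80% it is 70-74%.

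**2. What a single Year 1 value hides**

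Assume a constant hazard and linear waning from v0 at day 14 to v1 at day 365: VE(t) = v0 + (v1 − v0)(t − 14)/351. The Year 1 value is then about (v0 + v1)/2. Each quarter takes the value at its midpoint (days 52.5, 137, 228.5 and 319.5).

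| Assumed fall | Year 1 value | Q1 | Q2 | Q3 | Q4 |
|---|---|---|---|---|---|
| 95% to 75% | 85% | 93% | 88% | 83% | 78% |
| 95% to 50% | 72.5% | 90% | 79% | 68% | 56% |

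For example, Q4 in the second row is 0.95 − 0.45 × 305.5/351 = 0.558. The protocol gives no waning curve. Both rows show the mechanism and are not forecasts.

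**The case against.** The best defence is that the protocol sets no time scale for durability. Yearly VE over about three years is a coarse but coherent answer, in secondary objectives that are openly said to be possibly underpowered. Nothing is contradictory or miscalculated. That stands, and it makes this an improvement in method and not the correction of an error. It is not a detail left for a later analysis plan, because section 8.4 fixes the interval width itself.

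A second defence is the test-negative analysis by time since vaccination. Its specimens run from March 2021 through February 2022, so it falls almost entirely within about 13 months of dose 2, the window at issue. It would therefore be wrong to infer that the protocol looks at waning only by year. It still does not replace the cohort estimates: it is conditional on sample size, limited to selected variants, and takes up severe disease only if numbers suffice.

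Other stronger readings also lack support:

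- **Most two-dose person-time lies in Year 1.** This holds at the 4th interim under the assumed cuts. At the final analysis it needs further-dose uptake that the protocol does not state.
- **The incomplete Year 3 is a defect.** The average of 177 days is ordinary administrative censoring, which person-year rates and Cox regression handle.
- **Precision in narrow intervals is ample.** The protocol says "we expect to accrue 500,000 to 1,000,000 individuals receiving 2 doses of Moderna COVID-19 vaccine". With 500,000 per group and the section 9 rate of 2 hospitalizations per 1,000 in 4 months, a 3-month interval has 500,000 × 0.002 × 3/4 = 750 unvaccinated events, and 150 vaccinated events at VE 80%. The SE of the log HR is √(1/750 + 1/150) = 0.089, for a 95% CI of about 76-83%. This ignores censoring and assumes an equal comparator group, whereas section 6.2 expects too few unvaccinated members for 1:1 matching in later analyses. It is a best case.
- **Finer intervals isolate waning.** They do not by themselves separate waning from calendar waves, since each interval still mixes index dates spread over a year.

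**Conclusion.** The point holds for the cohort durability objectives. Secondary Objectives 12-13 cannot show change within the first 12 months after dose 2, and the conditional test-negative analysis does not fill that gap for diagnosis overall or for severe disease.

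It matters most at the 4th interim, where Year 1 holds roughly 78-96% of person-time and there is almost no durability contrast. That range rests on uniform second-dose dates, a cut between March and September 2022 and no further-dose censoring. At the final analysis Year 1 is one of three values and holds about 39-42% of planned person-time, or more if further doses censor many recipients. How much is hidden depends on the true waning. In the milder assumed case 85% stands for quarters running from 93% to 78%; in the steeper one about 72% stands for 90% to 56%.

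**What to change.** In section 8.4, for Secondary Objectives 12-13, estimate VE in intervals of about 3 months from day 14 through month 12 and of 6 months after that, where event counts allow. A spline for the time-varying log hazard ratio is an alternative. Apply this at both the 4th interim and the final analysis. Keep the yearly values as a summary. Report the number still at risk and the events in each group for every interval, so that thinning by further-dose censoring is visible.

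The cost is about one sentence in section 8.4 and extra table rows, with no new data. The downside is a wider confidence interval in each period, most of all for severe disease in later intervals, after censoring and with a smaller unvaccinated comparator group.
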